#### Potential Confounders and Effect Modifiers

In this descriptive summary of pregnancy episodes, no confounding adjustment is performed.

### Analyses

#### Specific Comparisons

No comparisons will be made. All database results will be presented independently, with no explicit comparisons across databases performed.

### Missing Data Handling

In this descriptive summary of pregnancy episodes, we assume the existence of pregnancy and the outcome to establish the cohorts. Patients with missing year of birth are excluded before inclusion into the OMOP CDM. Any unobserved diagnoses are regarded as absence of evidence.

### Data Preparation

The primary data quality assurance activities are performed through the development of OMOP CDM, which is documented elsewhere (<http://omop.org/CDM>).

### Statistical Analysis Plan

#### Descriptive Analyses

Counts of pregnancy episodes and distribution of outcomes will be produced for this study. Also distributions of pregnancy terms by outcome will be reviewed.

#### Quantitative Analyses

This is a methodologic study, so no quantitative comparisons will be made.

#### Sensitivity and Other Supplementary Analyses

No pre-specified sensitivity analysis will be performed.

### Data Quality Assurance

#### Validation Procedures

The primary data quality assurance activities are performed through the development of OMOP CDM, which is documented elsewhere (<http://omop.org/CDM> ).

The analysis will be programmed by a member of the Janssen Global Epidemiology Analytics team. A second programmer will perform an independent quality assurance review of all source code and analysis results to confirm the work performed is consistent with what is described in this protocol before the results are shared with the investigator team.

Validation efforts will include a review of 50 CPRD and 50 Optum randomly drawn pregnancy episodes from each outcome (6 outcomes X 50 X 2) for a total of 600 profiles by clinical personnel. An extra 50 profiles for LB outcomes for each database will also be reviewed because the majority of pregnancy episodes result in a live birth. Proportion of episodes which refer to an actual pregnancy, proportion of episodes with correct outcome and proportion of episodes with correct start date (or plausible start date if inferred) for each database will be determined.

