# SYNOPSIS

**LAY SUMMARY**

Administrative claims databases and electronic health records (EHR) are valuable resources for pregnancy research since pregnant women are excluded from randomized clinical trials (RCTs). In general, direct measures of gestational age are not available in claims databases and EHRs and an algorithm based on data available must be developed and validated in order to define the entire pregnancy episode from start to pregnancy outcome.

Our aim is to develop an algorithm to define pregnancy episodes for a network of population-based databases using the OMOP Common Data Model (CDM). We will attempt to identify all possible pregnancy outcomes with the algorithm, including live birth (at least one), stillbirth, delivery record only, trophoblastic disease, ectopic pregnancy, induced abortion and spontaneous abortion. Pregnancy episode start dates will be inferred with various pregnancy markers such as last menstrual period and nuchal ultrasound dates.

Our publication strategy will involve disseminating the algorithm methods and results from the electronic profile validation through a journal which focuses on epidemiology and/or drug safety. The validation should provide insight into the accuracy of various operating characteristics of the algorithm, such as start date inferral and outcome assignment. Validation results will be presented separately for each database in one publication in order to highlight the fact that it was possible to use one algorithm for all databases converted to the CDM at Janssen.

INTRODUCTION

Administrative claims databases and electronic health records (EHR) are valuable resources for pregnancy research since pregnant women are excluded from randomized clinical trials (RCTs). In general, direct measures of gestational age are not available in claims databases and EHRs and an algorithm based on data available must be developed and validated in order to define the entire pregnancy episode from start to pregnancy outcome.

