A study has not been performed that has attempted to accurately define pregnancy episodes including pregnancy start date on a network of population-based databases from the US and the UK using the OMOP Common Data Model (CDM). Using the CDM allows us to create one set of pregnancy concepts and one algorithm that can be applied to all data sources converted to the CDM, despite disparate native source code dictionaries and data structures found within each database. Additionally, prior observational data studies in which pregnancy episodes were identified have either been based upon populations that were potentially not generalizable or have only examined live birth outcomes. It is important to examine all possible outcomes (e.g. spontaneous and induced abortion, stillbirth, ectopic pregnancies etc.) as patient characteristics, prescribing patterns etc. in these populations may be dissimilar from patterns in pregnancies ending in live births.

OBJECTIVES

Our aim is to define pregnancy episodes and their outcomes (all possible outcomes including live births, stillborn, spontaneous and induced abortion, ectopic pregnancies etc.) within 3 US-based administrative claims databases: Truven MarketScan Commercial Claims and Encounters (CCAE), Truven MarketScan Multi-state Medicaid (MDCD), and the Optum ClinFormatics (Optum) database and the Clinical Practice Research Datalink (CPRD) which is a UK based general practice electronic health record.

These will be validated with review of 50 CPRD and 50 Optum randomly drawn pregnancy episodes from each outcome (6 outcomes X 50 X 2) for a total of 600 profiles by clinical personnel. Proportion of episodes by outcome which refer to an actual pregnancy, proportion of episodes by outcome with correct outcome, and proportion of episodes by outcome with correct start date (or plausible start date if inferred) for each database will be determined.

OVERVIEW OF STUDY DESIGN

This study follows a retrospective cohort design. 7 pregnancy episode outcome cohorts will be created and characterized from women with any pregnancy markers or outcomes:

- Live birth (at least one)
- Stillbirth
- Delivery-Live birth or stillbirth
- Trophoblastic Disease
- Ectopic pregnancy
- Induced abortion
- Spontaneous abortion

Women are allowed multiple pregnancy episodes.

STUDY POPULATION

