## OVERVIEW OF STUDY DESIGN

### Study Design

This study follows a retrospective cohort design. 7 pregnancy episode outcome cohorts will be created and characterized from women with any pregnancy markers or outcomes:

- Live birth (at least one)
- Stillbirth
- Delivery-Live birth or stillbirth
- Trophoblastic Disease
- Ectopic pregnancy
- Induced abortion
- Spontaneous abortion

Women are allowed multiple pregnancy episodes and the unit of analysis will be the pregnancy episode. Valid pregnancy outcomes for each patient will be chosen using an algorithm that utilizes an outcome assessment hierarchy, i.e. live births are assessed for validity first for each patient, any that are too close to another live birth are discarded. Still births for the same patient are then assessed to see if they are too close to all prior assessed live births and any other valid still births etc. Start dates will be assigned using pregnancy markers in a hierarchical fashion also (last menstrual period date records considered as start of pregnancy first, next considered are gestational age estimate records, etc.) See page 12 for a full description of the algorithm.

In medical practices, pregnancy episodes traditionally begin with the last menstrual period date and end with the birth outcome date as defined by the algorithm. The first trimester is defined as week 1-13, 2^nd^ trimester week 14-26 and 3^rd^ trimester week 27-40. For our episodes, the first two weeks of the first trimester will be defined as a pre-exposure period as conception most likely does not happen prior to this time.

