7. Next, spontaneous abortion (SA) outcomes will be assessed against all valid LB, SB, DELIV, TRO, ECT, AB, and SA outcomes in the same manner as described above for SB and added to the valid outcome set if Table 1 criteria is met. In order to eliminate SA rule-out diagnoses, if there is an antenatal GP visit, pregnancy confirmation or pregnancy complication record within 42 days of the SA record that ECT outcome will not be added to the valid outcome set.

| Table 1: Minimum Number of Days Required to Identify Separate Pregnancy Outcomes | | |
| --- | --- | --- |
| First Pregnancy Outcome | Second Pregnancy Outcome | Minimum Days Between Outcomes |
| LB | LB | 182 |
| LB | SB | 168 |
| LB | DELIV | 168 |
| LB | TRO | 70 |
| LB | ECT | 70 |
| LB | AB | 70 |
| LB | SA | 70 |
| SB | LB | 182 |
| SB | SB | 168 |
| SB | DELIV | 168 |
| SB | TRO | 70 |
| SB | ECT | 70 |
| SB | AB | 70 |
| SB | SA | 70 |
| DELIV | LB | 182 |
| DELIV | SB | 168 |
| DELIV | DELIV | 168 |
| DELIV | TRO | 70 |
| DELIV | ECT | 70 |
| DELIV | AB | 70 |
| DELIV | SA | 70 |
| TRO | LB | 168 |
| TRO | SB | 154 |
| TRO | DELIV | 154 |
| TRO | TRO | 56 |
| TRO | ECT | 56 |
| TRO | AB | 56 |
| TRO | SA | 56 |
| ECT | LB | 168 |
| ECT | SB | 154 |
| ECT | DELIV | 154 |
| ECT | TRO | 56 |
| ECT | ECT | 56 |
| ECT | AB | 56 |
| ECT | SA | 56 |
| AB | LB | 168 |
| AB | SB | 154 |
| AB | DELIV | 154 |
| AB | TRO | 56 |
| AB | ECT | 56 |
| AB | AB | 56 |
| AB | SA | 56 |
| SA | LB | 168 |
| SA | SB | 154 |
| SA | DELIV | 154 |
| SA | TRO | 56 |
| SA | ECT | 56 |
| SA | AB | 56 |
| SA | SA | 56 |

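### The profile review is sized for six outcomes and 600 profiles, but the protocol defines seven outcomes, and the total and the scope of the accuracy claim are not reconciled with that

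*Protocol*

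**What the plan says.** The review is described twice. Validation Procedures states: "Validation efforts will include a review of 50 CPRD and 50 Optum randomly drawn pregnancy episodes from each outcome". The sampling clause runs on to its total, "randomly drawn pregnancy episodes from each outcome (6 outcomes X 50 X 2) for a total of 600 profiles by clinical personnel", which gives the multiplication as six outcomes by 50 by two, or 600. The Objectives part of the Synopsis carries the same figure: "6 outcomes X 50 X 2) for a total of 600 profiles by clinical personnel". Validation Procedures goes on to add to the sample: "An extra 50 profiles for LB outcomes for each database will also be reviewed". The reason given is that most episodes end in a live birth. The Synopsis does not mention this addition.

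On the number of outcomes, Study Design says "7 pregnancy episode outcome cohorts will be created and characterized from women with any pregnancy markers or outcomes" and lists them. The Synopsis has the same list of seven. The last outcome step of the algorithm confirms the count: "spontaneous abortion (SA) outcomes will be assessed against all valid LB, SB, DELIV, TRO, ECT, AB, and SA outcomes". Tables 1, 2 and 4 carry the same seven codes.

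On databases, the study uses four: CCAE, MDCD, Optum and CPRD. The Lay Summary says: "Validation results will be presented separately for each database in one publication". It gives the purpose as showing that a single algorithm could be used in every database the sponsor has converted to the common data model. The Primary Objective is to evaluate the algorithm across all applicable databases in the sponsor's network.

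**The concern.** The sampling sentence contradicts itself once it is set beside the outcome list. It promises a draw from every outcome, but its multiplier counts one fewer than the protocol defines. No section says that an outcome is left out of the review or that two are pooled. Whoever draws the sample cannot tell whether to take six or seven strata, or which to drop.

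This matters because evaluating the algorithm is the primary objective and the profile review is the only planned measure of whether an episode is a real pregnancy with the right outcome and start date. No sensitivity analysis is planned and medical records will not be abstracted. The data-model quality work and the second programmer's review check conversion and code, not clinical correctness. The Synopsis asks for the accuracy proportions by outcome, so an outcome without a sample would have no estimate. Another outcome's result could not stand in for it, because the rules differ by type: trophoblastic disease, ectopic pregnancy and spontaneous abortion have rule-out logic that the others lack.

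A second, smaller issue is scope. Review takes place in two databases, while the Lay Summary and Primary Objective are framed around all of them.

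**Working it through.** **Inputs.** Profiles per outcome per database: 50 (Synopsis, Objectives; Validation Procedures). Databases reviewed: 2, CPRD and Optum (same places). Outcomes in the stated multiplier: 6 (same places). Outcomes defined: 7 (Synopsis; Study Design; algorithm step 1; Tables 1, 2 and 4). Extra live-birth profiles: 50 per database (Validation Procedures only). Study databases: 4 (Inclusion Criteria).

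**Formula.** Profiles = outcomes x profiles per outcome x databases reviewed, plus any extra live-birth profiles.

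**The plan's own figure.** 6 x 50 x 2 = 600. The product is right; the question is whether 6 is the right input.

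**With the defined outcomes.** 7 x 50 x 2 = 700. The difference is 700 - 600 = 100 profiles, and 100 / 600 = 16.7% above the stated figure. Conversely, spreading 600 evenly over seven outcomes and two databases gives 600 / 14 = 42.9, about 43 per outcome and database instead of 50.

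**With the extra live births.** If the addition applies to the two reviewed databases, it is 50 x 2 = 100.

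| Outcomes reviewed | Base sample | Extra live births | Total |
| --- | --- | --- | --- |
| 6 | 600 | 100 | 700 |
| 7 | 700 | 100 | 800 |

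If the addition were meant for all four databases it would be 50 x 4 = 200, giving 800 or 900. The two-database reading fits the rest of the section better, since only CPRD and Optum are sampled. Neither total is printed anywhere.

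**Database scope.** Two of four databases are reviewed. Full review at the same rate would need 7 x 50 x 4 = 1,400 profiles, or 1,400 + 200 = 1,600 with the extra live births. The protocol itself gives reasons not to assume that accuracy carries over. About half of CPRD live births have a last menstrual period value, but no US claims live births do (Pregnancy Episode Start Date Calculation). The screening-test timing was assessed in Optum (Table 3), and MDCD is a Medicaid population (Data Sources).

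**The case against.** The strongest reply is that the sampling sentence itself says episodes come from every outcome. Read that way, all seven are reviewed, and the 6 and the 600 are a counting slip. This stands. A reader might infer that one outcome certainly goes unvalidated, but the documents do not establish that: they contain a contradiction, not a stated omission. The slip still needs correcting, because the printed total is the figure that the reviewers' workload will be built on.

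Second, the added live-birth profiles are labelled as extra to the base sample, so they do not contradict 600 within Validation Procedures. This also stands. What remains is that the Synopsis leaves them out and that no sum is given.

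Third, reviewing CPRD and Optum is an openly stated choice of one health-record source and one claims source, and the factor of two matches it. References to each database in the sampling text can naturally mean those two. The Lay Summary's claim can be read as being about using one algorithm everywhere rather than as a promise of profile review everywhere. Much of this stands, so the two-database design is not an error. A reader might combine six outcomes with two databases and infer that only 12 of 28 outcome-by-database combinations are covered. That mixes an unproved omission with a disclosed choice; if every outcome is sampled, all 14 combinations in the two databases are covered. What survives is that the planned episode counts, outcome distributions and term distributions do not measure accuracy. Nothing in the text limits an accuracy conclusion to the databases reviewed.

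Finally, a reader might notice that 600 + 100 equals 7 x 50 x 2 and suggest moving the extra live-birth profiles to the seventh outcome. The equality is a coincidence. The protocol gives a reason for the larger live-birth sample, and the move would override it.

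**Conclusion.** The point holds as an inconsistency that should be fixed before sampling. The stated validation sample contradicts the outcome list: 600 is 100 short of the 700 that a draw of 50 from each of seven outcomes in two databases requires. With the extra live births, the total is 800 if seven outcomes are reviewed and 700 if six are. These totals assume that the extra profiles are for CPRD and Optum only. Whether an outcome is left out, merged or merely miscounted cannot be decided from the protocol. Only if six is really intended does one outcome lack its own accuracy estimate.

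The scope point holds in a limited form: the planned review can support accuracy statements for CPRD and Optum, not for CCAE or MDCD. The study is descriptive with no tests, so no power or error-rate claim is affected.

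**What to change.** In both the Synopsis (Objectives) and Validation Procedures, do one of the following:

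- Change six outcomes to seven and give one total: 700 plus 100 extra live births, 800 in all. The cost is 100 more profiles than the 700 implied by the current count with its extra live births.
- If only six are to be reviewed, name the outcome that is excluded or the two that are merged, report it as unvalidated or pooled, and state the total as 700. This adds no review work, but it leaves that outcome without its own accuracy estimate.

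In either case, add the extra live-birth profiles to the Synopsis and say which databases they come from.

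In the Lay Summary and the Primary Objective, limit the accuracy conclusion to CPRD and Optum, and label CCAE and MDCD results as not validated by profile review. This is a change of wording only; it narrows what the publication can claim.

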## STUDY LIMITATIONS

Truven CCAE and Medicaid and Optum databases only capture information reported through the payer, so any non-reimbursable exposures or health service utilization from other sources may not be observed in these data sources. In CPRD the general practices receive information from patient specialist visits but are not required to enter the data if it is not needed to inform future patient care. Births that do not occur in an inpatient setting most likely will not be captured in a claims database. Entire pregnancy episodes may not be captured by our algorithm, especially miscarriages occurring early in the pregnancy that require no medical care. Misclassification of outcomes could occur due to ambiguous outcome source codes.

**APPENDIX 1: Disease and Drug Codes**
